## Abstract

**Background:**

The forefoot and rearfoot can individually contribute to the development of chronic ankle instability (CAI) after an ankle injury. The aim of this study is to evaluate the effects of targeted forefoot and rearfoot stability training on dynamic balance, postural stability, gait biomechanics, and self-reported joint function in individuals with CAI.

**Methods:**

This study is a prospective, single-center, interventional, randomized controlled trial with two comparison groups, either a usual balance training group or a control group. Individuals (18–44 years) with a self-reported ankle instability, a history of at least one ankle injury at least 12 months ago with typical signs of inflammation, two or more episodes of “giving way” within the previous 6 months, and a Cumberland Ankle Instability Tool score ≤ 24 are included. Exclusion criteria include acute injury, lower extremity surgery or fracture, neurological disease, chronic overuse injuries such as Achilles or patellar tendinopathy, and current participation in a targeted ankle rehabilitation program. The primary outcome measures are dynamic balance as measured by the Y-Balance Test and postural stability as assessed by the Modified Balance Error Scoring System. Secondary outcome measures include gait biomechanics measured by 3D gait analysis and self-reported ankle function assessed by the Foot and Ankle Ability Measure.

**Discussion:**

Since there is a lack of information regarding the effects of targeted forefoot and rearfoot exercises on ankle stability, this study has the potential to improve future treatment plans and provide healthcare practitioners with an alternative treatment for CAI.

**Trial registration:**

DRKS (German Clinical Trials Register)—DRKS00034295, retrospectively registered on May 22, 2024 (Reason: The study was originally designed as a randomized controlled pilot study; therefore, the first participants were enrolled without registering the study, which was then caught up as soon as possible); URL: https://drks.de/register/de/trial/DRKS00034295/preview.

## Introduction

### Background and rationale {9a}

With an incidence of 1:10,000 people per day, a lateral ligament injury is the most common sports injury. Lateral ligament injuries can also occur during everyday activities [1]. For basketball players, it has been found that approximately 90% of the injured players are under the age of 40, and more men than women suffer from ligament injuries [2]. Approximately 32–74% of individuals experience recurrent symptoms such as reinjury or persistent ankle instability [3, 4]. In 40–70% of cases, chronic ankle instability (CAI) is the result of an injury to the capsule-lateral ligament apparatus [5].

CAI is characterized by a history of ankle injury with typical signs of inflammation, a “giving way” or feeling of instability, and relevant limitations in the patient’s daily activities [6]. In addition, using the Short-Form-36 questionnaire (SF-36), it has been found that individuals with CAI have a significantly reduced quality of life compared to those without CAI. Biomechanical studies have shown deficits in gait and postural control/balance [7–9]. In the first half of the stance phase, there is an increased rearfoot inversion angle, which results in more rolling over the lateral border of the plantar foot. This leads to increased stress in this area and enhances the risk of a recurrent ankle sprain [7, 10, 11]. The altered foot rollover also affects knee joint kinetics in the early gait cycle, i.e., increased knee abduction moment, as well as ankle joint kinetics and muscle activity in the late gait cycle, i.e., increased eversion moment and peroneal muscle activity to compensate for the maladaptive gait pattern [7].

The interaction between rearfoot and forefoot individually contributes to the development of chronic ankle instability following an ankle injury [12]. A variety of joint movements can be observed in participants with chronic ankle instability:Increased eversion and joint play during internal talocrural rotation of the rearfootIncreased flexion motion of the forefoot relative to the rearfoot and first metatarsophalangeal jointHypomobility of forefoot inversion

Fraser et al. observed increased rearfoot inversion 2 weeks after a lateral ankle sprain (LAS) [12]. This modified movement following an LAS can be considered a preliminary CAI [13]. Furthermore, increased forefoot eversion has been shown to be associated with greater laxity in the metatarsal joints and the fibularis longus muscle [14]. The interaction of altered biomechanics and a lack of therapeutic and/or medical intervention following LAS has been found to result in CAI [15].

During normal slow walking, foot lengthening flattens the medial arch to improve ground contact and balance control [16]. During fast walking, foot lengthening in the stance phase is reduced due to increased longitudinal arch stiffness to improve pushing off the foot by optimizing the lever arm. The symptoms described above can disrupt these normal foot biomechanics during gait and promote functional deficits in patients with CAI. Deficits in patients with CAI have been identified using magnetic resonance imaging of the muscles in the affected leg and foot. Both the muscles of the posterior superficial compartment and the small foot muscles have reduced muscle volume compared to healthy participants [17].

Non-surgical treatment is recommended for CAI [18]. Standard care includes balance training, ankle strengthening, and flexibility exercises. Training approaches for postural stability are stabilization exercises [18, 19]. These should be performed first on a flat surface, then on an unstable surface such as the wobble board, and then with additional coordinative-cognitive demands such as closed eyes. Gait training is also recommended [18]. The standard treatment, balance training with a wobble board, and therefore the comparator in this study, is limited by the inability to specifically control the numerous articulations between the rearfoot, midfoot, and forefoot that are important for the functional coupling of the forefoot and rearfoot. This is necessary to prevent potential sequelae such as the development of osteoarthritis [15]. The limitations of balance training described above may be overcome by supplementing it with targeted forefoot and rearfoot training. There is still a lack of information on the effects of targeted forefoot and rearfoot training to improve ankle function. Two studies have been conducted that compared lower extremity muscle activity while standing on various unstable training devices [20, 21]. Additionally, one single-case experimental study examined the effects of targeted rearfoot and forefoot training on dynamic balance and joint function in three soccer players [22].

In the study by Sánchez-Barbadora et al. [20], the muscle activity of lower extremity muscles was measured in 20 healthy active subjects using various balance training devices (BOSU, wobble board, power board, and Blackboard). The balance training devices were divided into two categories: global balance devices, such as the BOSU, wobble board, power board, and a balance training device that distinguishes between the forefoot and rearfoot, such as the Blackboard. Surface electromyography (sEMG) was used to record the activity of the peroneus longus (PL), peroneus brevis (PB), soleus (SOL), gastrocnemius medialis (GM), gastrocnemius lateralis (GL), and tibialis anterior (TA) muscles. All tests were carried out in a standing position and in a single-leg squat position on each balance training device. The Blackboard was only tested with an unstable rearfoot position. All tests showed similar activation of the PL muscle on each device. For all other muscles, the activation for standing or squatting on the Blackboard was lower than for the devices designed for global instability.

In another study, Alfuth and Gomoll [21] examined the muscle activity of the lower extremities of 27 healthy adults under one stable and five unstable conditions. The Mini Stability Trainer (ARTZT vitality®, Ludwig ARTZT GmbH, Dornburg, Germany) was used for four of the unstable conditions with various modifications, and the Balance Pad (BP) was used for one of the unstable conditions. Surface electromyography (sEMG) was used to record the activity of the TA, PL, SOL, GM, long head of the biceps femoris (BF), and vastus medialis (VM) muscles. The TA, PL, and BF muscles demonstrated significantly higher mean activity under the BP condition and the forefoot unstable in the frontal plane and multidirectional conditions compared with the control condition. The PL muscle exhibited significantly higher mean activity under the rearfoot unstable in the frontal plane condition. The SOL exhibited significantly higher levels of activity when balancing on the BP. The VM muscle exhibited significantly higher activity levels under conditions involving forefoot instability in the frontal plane and multidirectional movement.

In a single-case experimental study conducted by Alfuth and Schroers [22], three soccer players participated in a 6-week training program using the Mini Stability Trainer. The participants were divided into two groups: one that began with forefoot training and one that began with rearfoot training. The training modalities were changed after 3 weeks. Measurements were taken before the training program began, after 3 weeks, and after an additional 3 weeks. The two subjects who started with forefoot training exhibited no changes in the Cumberland Ankle Instability Tool (CAIT) after 3 weeks. After 6 weeks and transitioning to rearfoot training, the players demonstrated improvements of approximately 1 and 5 points, respectively. The third participant began the program with rearfoot training and subsequently improved by three points on the CAIT after 3 weeks. After transitioning to forefoot training and completing an additional 3 weeks, they demonstrated a 2-point increase in CAIT scores. All players demonstrated an enhancement in Foot and Ankle Outcome Score values following a 3-week period, with an additional enhancement after 6 weeks. In the YBT, the players demonstrated marginal improvements.

### Explanation for the choice of comparator {9b}

The study comprises three comparison groups. The initial intervention is constituted by training with the Mini Stability Trainer. The Mini Stability Trainer facilitates targeted training of the forefoot and rearfoot. The targeted joints are of particular importance for the functional coupling of the forefoot and rearfoot. This is necessary to prevent possible consequences such as the development of osteoarthritis [15]. The second group is the standard treatment, which consists of balance training with a Wobble Smart Board. The primary objective of the study is to determine the comparative efficacy of the novel training intervention employing the Mini Stability Trainer in comparison to the conventional standard treatment. The second comparison is a control group without any training to assess if training with the Mini Stability Trainer is more effective than no training at all.

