### Objectives {10}

The study will be guided by the following specific objective: To determine whether the outcomes of dynamic balance, postural stability, gait biomechanics, and joint function improve in the intervention group and the balance training group after a 6-week intervention period and whether there is a significant difference compared to the control group.

The study is also based on the following hypotheses:The intervention group and the balance training group will lead to similar significant improvements in outcomes compared to the control group.It is also hypothesized that there will be no significant differences between the intervention group and the balance training group.

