Study type	Allocation: randomized; model: parallel allocation; intervention description: comparison of clinical outcome measures at four time points between three cohorts (Wobble Smart Board, Mini Stability Trainer, control group) of subjects with chronic ankle instability (CAI ^b^), whether the two intervention groups reduce the primary and secondary outcome measures compared to the control group; blinding: single-blind; blinding description: the principal investigator analyzing the results will be blinded to group allocation; different investigators will be used to perform the intervention and to analyze the results
Primary outcomes	Dynamic balance and postural stability using the Y-Balance Test (YBT ^c^) and Modified Balance Error Scoring System (MBESS d)
Secondary outcomes	Gait biomechanics using 3D gait analysis (e.g., ankle abduction and adduction; knee varus/valgus position; spatiotemporal parameters); ankle function using the Foot and Ankle Ability Measure (FAAM ^e^)

^a^*CAIT *Cumberland Ankle Instability Tool; ^b^*CAI *chronic ankle instability; ^c^*YBT *Y-Balance test; ^d^*MBESS *Modified Balance Error Scoring System; ^e^*FAAM *Foot and Ankle Ability Measure

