## Statistical methods

### Statistical methods for primary and secondary outcomes {27a}

Primary and secondary outcome measures are reported descriptively using mean ± SD or median and interquartile range according to their type (e.g., ordinal or interval scale). After testing the data for normal distribution using the Shapiro-Wilk test and histograms, for the primary outcomes of dynamic balance (YBT) and postural stability (MBESS), the significance of differences in post-intervention change within and between groups will likely be analyzed using repeated measures analysis of variance (ANOVA) (YBT) or Friedman tests or Kruskal-Wallis tests (MBESS) and post hoc tests with Bonferroni correction to account for multiple testing. After testing the data for normal distribution using the Shapiro-Wilk test and histograms, for the secondary outcome of gait biomechanics, the significance of differences in post-intervention change within and between groups will likely be analyzed using repeated measures analysis of variance (ANOVA) and post hoc tests with Bonferroni correction to account for multiple testing. For the secondary outcome of joint function (FAAM), the significance of differences in post-intervention change within and between groups will be analyzed using Friedman tests or Kruskal-Wallis tests and post hoc tests with Bonferroni correction to account for multiple testing. The global significance level is set to *α* = 0.05. No additional analyses are planned.

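### The protocol names Mini Stability Trainer versus wobble board as its primary objective in one section and training versus control as its question in others, and nothing settles which contrast decides the trial

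*Protocol article*

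**What the plan says.** The protocol article describes the question in several places.

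- **Explanation for the choice of comparator {9b}**: "The primary objective of the study is to determine the comparative efficacy of the novel training intervention employing the Mini Stability Trainer in comparison", with wobble-board training, the usual care, as the reference. A further sentence gives control a lower place: "The second comparison is a control group without any training to assess if training with the Mini Stability Trainer is more effective than no training".
- **Objectives {10}**: one specific objective, namely whether the outcomes improve in both trained groups and "whether there is a significant difference compared to the control group". Mini versus wobble is not part of that objective. It enters through the hypotheses: the first expects that "The intervention group and the balance training group will lead to similar significant improvements in outcomes compared to the control group", the second that "there will be no significant differences between the intervention group and the balance training group".
- **Table 1, study type row (Trial design {12})**: "whether the two intervention groups reduce the primary and secondary outcome measures compared to the control group".
- **Discussion**: repeats the expectation that both trained groups improve and do not differ significantly from each other.
- **Sample size {19}**: 33 participants (11 per group) to detect a mean difference of 4.6% in the Y-Balance Test (YBT) composite, with f = 0.33, power 0.9 and alpha 0.05, raised to 36 (12 per group). It does not say which groups the 4.6% separates.
- **Statistical methods {27a}**: repeated measures ANOVA for the YBT, Friedman or Kruskal-Wallis tests for the Modified Balance Error Scoring System (MBESS), then "post hoc tests with Bonferroni correction to account for multiple testing". No pair is singled out.

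No section says whether Mini versus wobble is a superiority, non-inferiority or equivalence question, and no margin is given.

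**The concern.** The contrast that {9b} calls primary is absent from the objective in {10} and from the question in Table 1, and the protocol expects it to be null. A reader of the final report could therefore not tell from the protocol which comparison the trial was meant to settle. With one data set, a report built on {10} might lead with a significant benefit of training over no training, while a report built on {9b} would have to lead with an unresolved comparison of two devices.

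The second hypothesis adds a further difficulty. It is phrased as an absence of significance, which a non-significant test cannot confirm without a margin and enough precision. If Mini versus wobble is primary, the planned test does not answer the question in the form in which the protocol expects the answer.

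**Working it through.** **1. Does the sample size reveal the deciding contrast?**
Inputs from {19}: f = 0.33, N = 33, three groups, alpha 0.05, power 0.9. The two time points for the YBT come from {16}. Assumed: pre-post correlation 0.5, which is not stated.

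For the group-by-time interaction, lambda = N × f² × 2/(1 − rho) = 33 × 0.1089 × 4 = 14.37, with 2 and 30 degrees of freedom. Power is 0.907, and N = 30 gives 0.874, so the stated 33 is reproduced. It is the size for an omnibus test over three groups and favours no pair.

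**2. Change SD implied by these figures**
The effect size on change scores is √(14.37/33) = 0.66. If both trained arms gain d over control (the pattern in the first hypothesis), the SD of the three means is d × √2/3. Then d/SD = 0.66 × 3/√2 = 1.40, and with d = 4.6 the SD is 4.6/1.40 = 3.29. This value rests on the assumed correlation and pattern of means, so SDs of 4.6 and 5.8 are shown as well.

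**3. How often do the two candidate contrasts give different answers?**
Simulation for the YBT: 200,000 trials per SD, 12 per arm, change means (4.6, 4.6, 0), F test at 0.05, then pooled-variance pairwise t tests at 0.05/3. Three pairs are an assumption, because {27a} does not give the number.

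| Change SD (assumed) | Mini vs control significant, Mini vs wobble not |
|---|---|
| 3.29 | 80% |
| 4.6 | 47% |
| 5.8 | 29% |

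Mini versus wobble is significant in about 1.7% of trials, as it should be when the true difference is zero and the level is 0.05/3.

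**4. What would a non-significant Mini versus wobble result show?**
The 95% CI half-width is t(0.975; 33) × SD × √(2/12) = 2.0345 × 0.408 × SD = 0.831 × SD:

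- SD 3.29: 2.7 points
- SD 4.6: 3.8 points
- SD 5.8: 4.8 points

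The target difference is 4.6. Even at the smallest SD, a true difference of half the target (2.3 points) would be missed in 63% of trials at 0.05 and in 79% at 0.05/3 (two-sample t, 22 df). With an assumed non-inferiority margin of 2.3 points, one-sided 0.025 and 90% power, n per arm = 2 × (1.96 + 1.28)² × (3.29/2.3)², about 43, against 12 planned.

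**5. What would ordering the tests change?**
Power of Mini versus control on the YBT (noncentral t, 33 df, 12 per arm):

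| Change SD | At 0.05/3 | At 0.05 |
|---|---|---|
| 3.29 | 0.81 | 0.91 |
| 4.6 | 0.48 | 0.66 |
| 5.8 | 0.30 | 0.47 |

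This gain comes from the testing rule, not from removing the contradiction.

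**The case against.** A reader might infer that the result the protocol expects would be a failure under {9b} and a success under {10}. The documents do not support that. Comparative efficacy has no direction, and a null Mini versus wobble result is what {10} and the Discussion predict. Background {9a} says the limits of balance training may be overcome, which hints at superiority. But it speaks of supplementing balance training, whereas the trial sets one device against the other. What remains is that no type of comparison is stated and that similarity cannot be read from a non-significant test.

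A reader might also infer that the verdict could be picked afterwards at the cost of false positives. Within one outcome, Bonferroni correction over all the pairs guards against that. What stays open is which comparison is reported as the main one.

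The 80% is not a measure of harm. It is close to the power of Mini versus control (0.81) once Mini versus wobble is set to zero, and two different questions with different true answers will differ. The SD of 3.29 may also be low. The YBT section gives a minimum detectable change of 7.7 to 14%. If that is a 95% limit in the same units (an assumption), measurement error alone gives a change SD of 7.7/1.96 = 3.9 to 14/1.96 = 7.1, so 47% and 29% are more plausible than 80%.

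Finally, neither {10} nor Table 1 uses the word primary for training versus control, and a testing order may stand in an analysis plan that is not shown. That softens the conflict but does not remove it: an analysis plan can order tests, but it should not have to choose between objectives that the protocol states differently.

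**Conclusion.** The point holds as an inconsistency of objectives with no stated deciding contrast. It needs none of the assumed figures: {9b} against {10} and Table 1 is enough, and {19} and {27a} do not resolve it. The percentages (80, 47 and 29%) and half-widths (2.7 to 4.8 points) only illustrate what could follow for the YBT, under assumed SDs, equal gains of 4.6 points in both trained arms, 12 per arm and, for the percentages, three Bonferroni pairs. The sample size figure is not itself in error, and a null result between the devices is not shown to be a failure. This should be fixed.

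**What to change.** Before the analyst sees data by arm, name one deciding contrast and its type. Use it consistently in {9b}, {10}, Table 1, {19}, {27a} and the Discussion, for both primary outcomes (YBT and MBESS).

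- **If it is Mini versus control**, as the stated objective and hypotheses suggest: reword {9b} so that Mini versus wobble is secondary, report it as an estimate with a 95% CI, and claim no similarity from a non-significant test. Testing the named contrast first at 0.05 on the YBT is an option, with the power gain shown above. The existing Bonferroni approach is also valid. The cost of ordering is that later contrasts cannot be claimed if the first fails, and the multiplicity rule across YBT and MBESS must then be stated.
- **If Mini versus wobble stays primary**: say so in {10} and Table 1, state superiority, or non-inferiority or equivalence with a margin, and replace the hypothesis of no significant difference. The number of participants should then be checked against that aim.

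The first route costs wording and a registry update, with no extra participants. The second may show that 12 per arm is too few for the margin chosen.

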### Objectives {10}

The study will be guided by the following specific objective: To determine whether the outcomes of dynamic balance, postural stability, gait biomechanics, and joint function improve in the intervention group and the balance training group after a 6-week intervention period and whether there is a significant difference compared to the control group.

The study is also based on the following hypotheses:The intervention group and the balance training group will lead to similar significant improvements in outcomes compared to the control group.It is also hypothesized that there will be no significant differences between the intervention group and the balance training group.

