### How missing data will be handled in the analysis {27c}

If a participant is required to receive the other group’s treatment or switch to the control group (e.g., if they experience significant pain during exercise), or if values are missing for any reason (e.g., dropout or loss to follow-up), this is accounted for using ITT analysis. This means that participants are analyzed in the group to which they were randomized, and missing values are imputed. The imputation method (single or multiple imputation) is determined according to the guidelines of Jakobsen et al. [42] at the end of data collection.

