## Discussion

The purpose of this study is to evaluate the effects of targeted forefoot and rearfoot stability training on the primary measures of dynamic stability and postural stability, as well as the secondary measures of gait biomechanics and self-reported function on the CAI. We hypothesize that the targeted forefoot and rearfoot group, as well as the wobble board group, will show significant improvements in the aforementioned measures but will not show significant differences between these intervention groups. Since there is currently a lack of information regarding targeted forefoot and rearfoot exercises on ankle stability, this study has the potential to improve long-term outcomes regarding CAI and provide an alternative to healthcare practitioners in treatment. The data from this study could therefore be used in the future to develop treatment plans for CAI.

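### The two trainings are expected to be similar, but the only planned evidence is a non-significant difference test with 12 per arm, which cannot show similarity

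*Protocol article*

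**What the plan says.** Objectives {10} gives two linked hypotheses. First, both training groups "will lead to similar significant improvements in outcomes compared to the control group". Second, "there will be no significant differences between the intervention group and the balance training group". The Discussion repeats the prediction that the two groups "will not show significant differences between these intervention groups" and says the study may "provide an alternative to healthcare practitioners in treatment".

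The section on the choice of comparator {9b} states that the aim is to "determine the comparative efficacy of the novel training intervention employing the Mini Stability Trainer in comparison to the conventional standard treatment". It calls this the primary objective and describes the untrained control group as the second comparison. Objectives {10}, by contrast, gives a specific objective whose only named between-group comparison is with control.

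Statistical methods {27a} plans repeated measures ANOVA for the Y-Balance Test (YBT) and Friedman or Kruskal-Wallis tests for the Modified Balance Error Scoring System (MBESS), with Bonferroni-corrected post hoc tests. It closes by saying that no additional analyses are planned. Sample size {19} is set to detect a 4.6% difference in the YBT composite (f = 0.33, power 0.9, alpha 0.05): 33 participants, raised to 36, or 12 per group.

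**The concern.** A difference test can reject equality but cannot support it. A non-significant result arises when the arms are alike, and also when the trial is too small or too noisy to separate them. When the expected finding is itself worded as non-significance, poor precision counts in favour of the hypothesis: the noisier the data and the more dropouts, the more likely it is to be met.

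The protocol gives no margin and no interval criterion by which the arms could be judged similar. The contrast affected is the one that {9b} calls primary, and the practical message, that targeted training is an alternative to wobble-board training, leans on it. The trial could therefore report two trainings as alike when the data leave room for a difference as large as the one it was designed to find.

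**Working it through.** **1. Reproduce the stated sample size.** Inputs from {19}: f = 0.33, alpha 0.05, power 0.9, three groups, two time points. For the group-by-time interaction, λ = N·f²·m/(1 − ρ) with m = 2 and df = (2, N − 3). The protocol does not state ρ. With ρ = 0.5, λ = 33 × 0.1089 × 4 = 14.37 and power is 0.907; N = 30 gives 0.874. So N = 33 reproduces. It is the size for an omnibus test of difference, not for showing similarity.

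**2. SD of change.** The protocol does not give one, so two sources are used.

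- *Trial's own sizing.* With ρ = 0.5 the effect size on the change scale is 2 × 0.33 = 0.66, which is the SD of the group mean changes divided by the SD of change. If two groups are equal and one differs by 4.6, the SD of the means is 4.6 × √2/3 = 2.17, so the SD of change is 2.17/0.66 = 3.3. If the three means are evenly spaced across 4.6, it is 4.6/√6 = 1.88, so 1.88/0.66 = 2.8.
- *Minimum detectable change (MDC).* Outcomes {16} gives 7.7 to 14% for the YBT. If this is a 95% MDC, the SD of a retest difference is MDC/1.96: 7.7/1.96 = 3.9 and 14/1.96 = 7.1.

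**3. Training versus training, 12 per arm.** SE = SD × √(2/12) = 0.408 × SD, with pooled df = 36 − 3 = 33. The 95% CI half-width is 2.035 × SE. For the test, three Bonferroni contrasts are assumed (two-sided 0.05/3, critical t = 2.522), and the chance of non-significance comes from the noncentral t with noncentrality δ/SE.

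| SD of change | SE | 95% CI half-width | Non-significant if true difference is 4.6 | Non-significant if true difference is 2.3 |
|---|---|---|---|---|
| 2.8 | 1.14 | 2.3 | 7% | 68% |
| 3.3 | 1.35 | 2.7 | 19% | 78% |
| 3.9 | 1.60 | 3.3 | 36% | 85% |
| 7.1 | 2.92 | 5.9 | 81% | 95% |

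The 2.3-point column is half the design difference. Without any Bonferroni adjustment, the first two rows of that column become 50% and 62%.

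**4. What a margin would demand.** The protocol states none, so these are illustrations. Two one-sided tests at 5% with 90% power when the arms are equal need n = 2·[SD × (1.645 + 1.645)/margin]² per arm. At SD 2.8 to 3.3 (unrounded 2.85 and 3.29), a margin of 2.3 needs 34 to 45 per arm and a margin of 4.6 needs 9 to 12. Whether 12 per arm could show similarity on the YBT therefore depends on the margin.

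**The case against.** The strongest reply has three parts.

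*The wording is only an expectation.* No section gives a rule that turns non-significance into a declaration of equivalence, and the Discussion speaks only of potential. That is correct. A reader might infer that the protocol commits to reporting p above 0.05 as equivalence; it does not say so. The statement that no further analyses are planned is also illustrated in {27d} by subgroup and adjusted analyses, so it may not have been meant to exclude intervals. What remains is that the hypothesis is itself phrased as a test result, next to a prediction of similar improvement, and that no other means of judging similarity is named.

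*The trial may be precise enough.* On the SD implied by its own sizing, a full 4.6-point gap would be missed in only 7 to 19% of trials. The MDC comes from a cited source, reflects retest error, and is not tied to the composite score. This stands: it would be wrong to say that low power alone guarantees the hypothesis whatever the true difference. It does not rescue the inference for smaller differences, where non-significance is the usual outcome on either SD.

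*The planned analysis is standard.* Analysing participants as randomised is sound. A reader might infer from the provision "If a participant is required to receive the other group’s treatment or switch to the control group" that switching would pull the training arms together and so favour a finding of similarity. The documents do not support this: no switching rate is given, and a move from one training arm to control could widen the gap. A per-protocol analysis is therefore not required on this ground.

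**Conclusion.** The point holds as a fault of inference, not of arithmetic; N = 33 reproduces for the omnibus interaction at ρ = 0.5. The arm-to-arm hypothesis is framed so that a non-significant test is its only planned support, and with 12 per arm such a result is uninformative about differences around half the design effect (68 to 78% non-significant at SD 2.8 to 3.3; 85 to 95% at SD 3.9 to 7.1). For the full 4.6 points the answer depends on the SD: 7 to 19% or 36 to 81%.

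These figures assume ρ = 0.5 for the first SD range, a 95% MDC for the second, and a family of three contrasts. The protocol does not state the family size, so the per-contrast threshold of 0.05/3 is also an assumption. MBESS, the other primary outcome, has no sizing, so no comparable figure can be given for it.

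Separately, {9b} and {10} need to agree on which contrast decides the trial. This should be fixed before analysis, but it does not invalidate the design.

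**What to change.** - Reword the second hypothesis in {10} and the matching sentence in the Discussion. The difference between the two trainings will be estimated with a 95% confidence interval for each primary outcome (YBT, and MBESS with a suitable nonparametric interval), and a non-significant test will not be read as similarity.
- Permit the word similar only if the interval lies wholly within a margin that is clinically justified and fixed before the data are analysed; otherwise report the comparison as inconclusive. Do not adopt 4.6% by default, because it is the whole effect the trial was sized to detect.
- State in both {9b} and {10} which contrast decides the trial.

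The cost is a few sentences and one interval per primary outcome. Participants, planned tests and sample size need not change. The price is in the conclusion: the trial may have to report an inconclusive comparison where it expected to report no difference. With a tight margin that is likely, since an interval with a half-width of 2.3 to 2.7 points at best will not usually fit within ±2.3.
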